#### **5.4.2 Handling of Participant Withdrawals or termination**

Participants who discontinue PrEP, but otherwise will remain eligible for the study, will remain eligible for follow-up visits at their healthcare facility or bar workplace. Study team members will continue to reach out to these individuals by phone to invite them to scheduled follow-up visits – in order to capture any adverse events or unanticipated problems. Withdrawn or discontinued participants will not be replaced, since such events represent a meaningful endpoint for analysis.

### **5.5 Premature Termination or Suspension of Study**

This study may be temporarily suspended or prematurely terminated if there is sufficient reasonable cause. Written notification, documenting the reason for study suspension or termination, will be provided by the suspending or terminating party to [name], all funding agencies and all relevant IRBs. If the study is prematurely terminated or suspended, the PI will promptly inform the IRB and will provide the reason(s) for the termination or suspension.

Circumstances that may warrant termination or suspension include, but are not limited to:

- Determination of unexpected, significant, or unacceptable risk to participants

- Insufficient compliance to protocol requirements
- Data that are not sufficiently complete and/or evaluable
- Determination of futility

The study may resume once concerns about safety, protocol compliance, data quality are addressed and satisfy the sponsor, IRB and/or FDA.

## 6. STUDY AGENT

### 6.1 Study Agent(s) and Control Description

#### 6.1.1 ACQUISITION

MDH is the HIV implementing partner in Dar es Salaam region and they are also implementing the PrEP program in Ubungu Municipality following the National PrEP Framework. It is in view of this we have agreed to work with MDH in this trial so that we can integrate the trial with the PrEP program in the municipality.

#### 6.1.2 FORMULATION, APPEARANCE, PACKAGING, AND LABELING

Emtricitabine/Tenofovir disoproxil Mylan is available as a light green, film-coated, capsule shaped, biconvex tablet, of dimensions 19.80 mm x 9.00 mm, debossed with 'M' on one side of the tablet and 'ETD' on the other side. It is available either as a bottle or blister pack of 30 film-coated tablets. Emtricitabine/Tenofovir disoproxil Mylan is manufactured by Mylan Inc. and its subsidiary Matrix Laboratories Limited, and has been judged bioequivalent to Truvada. Emtricitabine/Tenofovir disoproxil Mylan is a commercially marketed product, and is available for humans in the form, route and dose planned in this trial.

#### 6.1.3 PRODUCT STORAGE AND STABILITY

Emtricitabine/Tenofovir disoproxil should be stored at 25 degrees Celsius, with excursions permitted to 15-30 degrees Celsius.

#### 6.1.4 PREPARATION

No preparation of Emtricitabine/Tenofovir disoproxil is required by either healthcare provider or participants.

### **6.1.5 DOSING AND ADMINISTRATION**

Emtricitabine/Tenofovir disoproxil will be dosed as a single tablet (containing 200 mg/300 mg of emtricitabine and tenofovir disoproxil fumarate) once daily taken orally with or without food.

### **6.1.6 ROUTE OF ADMINISTRATION**

The route of administration of PrEP will be oral only.

### **6.1.7 STARTING DOSE AND DOSE ESCALATION SCHEDULE**

1 tablet (200 mg/300 mg of emtricitabine and tenofovir disoproxil fumarate). No escalation.

### **6.1.8 DOSE ADJUSTMENTS/MODIFICATIONS/DELAYS**

None

### **6.1.9 DURATION OF THERAPY**

The therapy will last for six months.

### **6.1.10 TRACKING OF DOSE**

Dose/adherence monitoring will be based on self-reported use evaluated every month, as well as pill counts of remaining pills at each visit.

## **7. STUDY PROCEDURES AND SCHEDULE**

### **7.1 Study Procedures/Evaluations**

#### **7.1.1 STUDY SPECIFIC PROCEDURES**

- A medical history of each participant will be taken by clinicians at the sites. The history will include medication history including whether they are taking any over-the-counter medications. Based on this the Tanzanian healthcare provider will assess if they are taking any proscribed medications per WHO recommendations.

- A brief physical examination for vital signs, including height, weight and blood pressure will be completed by the clinical team.
- The clinical team will collect a finger-prick blood sample for point-of-care HIV and Hepatitis B surface antigen testing; , TDF testing for PrEP adherence, and will conduct a blood draw for laboratory-based serum creatinine, and syphilis testing.
- The results of all rapid tests will be provided to study participants at the time of testing. Serum creatinine tests will be discussed with participants if the results are abnormal.
- Standard HIV counselling will be provided to participants whether they test positive or negative, per national Tanzanian guidelines.

Adherence to emtricitabine/tenofovir disoproxil will be measured in three ways at each two-monthly visit. First, by self-reported adherence in terms of percentage of doses taken at the agreed time of day on the correct day. Second, by pill count of returned pills at the visit. Third, by a point-of-care urine assay for TDF. Patient-reported outcomes will be ascertained through a short questionnaire at each trial visit, in addition to the collection of baseline data prior to enrolment.

---

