### 7.3. Study Schedule

#### 7.3.1 SCREENING

##### Recruitment and Screening visit

- Recruitment of barmaids for screening and PrEP intervention
- Obtain informed consent of potential participant verified by signature on screening informed consent form.
- Conduct screening questionnaire.
- Obtain demographic information and medical, medication, alcohol and tobacco use history.
- Review medical history to determine eligibility based on inclusion/exclusion criteria.
- Review medications history to determine eligibility based on inclusion/exclusion criteria.
- Perform medical examinations needed to determine eligibility based on inclusion/exclusion criteria. Specifically we will perform:
  - A point-of-care HIV test as part of standard HIV counselling and testing;
  - A point-of-care Hepatitis B surface antigen (HBsAg);and
  - Blood sample collection for a local, laboratory-based test of serum creatinine and syphilis.
- Schedule study visits for participants who are eligible and available for the duration of the study.

- The screening visit will require between 1.5 and 2 hours to complete

---

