### **7.3.2 ENROLLMENT/BASELINE**

#### **Baseline Visit (Visit 0, Month 0)**

- Obtain informed consent of potential participant verified by signature on study informed consent form.
- Verify inclusion/exclusion criteria.
- Division into the two study randomization groups 1 and 2
- Directly observe the first dose of emtricitabine/tenofovir disoproxil being taken and provide 28 (1 month) days of emtricitabine/tenofovir disoproxil.
- Counsel participant on adherence to emtricitabine/tenofovir disoproxil and need to contact the study if any changes in health arise.
- Conduct baseline questionnaire

---

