### **7.3.3 FOLLOW-UP**

#### **Refill Visit 1 (Visit 1 Day 30 +/- 7; Month 1)**

- Provide additional 28-days (1 month) supply of medication to the participant
- Check on adverse effects
- Adherence Counselling
- Test for HIV

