#### **Follow-up Visit 1 (Visit 2, Day 60 +/- 7; Month 2)**

- Record adverse events as reported by participant or observed by investigator.
- Record vital signs, results of screening for Syphilis or other health conditions.
- Conduct urine tests TDF testing for adherence.
- Provide additional 28-days (1 month) supply of medication to the participant
- Record participant's adherence to treatment program.

- Re-counsel the participant on adherence to emtricitabine/tenofovir disoproxil and need to contact the study if any changes in health arise.
- Visit 2 will require between 1.5 and 2 hours to complete

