#### **Follow-up Visit 2 (Visit 4, Day 120 +/- 7; Month 4)**

- Record adverse events as reported by participant or observed by investigator.
- Record vital signs, or other health conditions.
- Conduct HTC including a rapid HIV test.
- Provide additional 28-day (1-month) supply of medication to the participant
- Record participant's adherence to treatment program.
- Re-counsel the participant on adherence to emtricitabine/tenofovir disoproxil and need to contact the study if any changes in health arise.
- Visit 4 will require between 1.5 and 2 hours to complete

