### **7.3.4 FINAL STUDY VISIT**

#### **Final Study Visit (Visit 6, Day 180 +/- 7; Month 6)**

- Record adverse events as reported by participant or observed by investigator.
- Record vital signs or other health conditions.
- Collect blood for creatinine and syphilis testing.
- A point-of-care Hepatitis B surface antigen (HBsAg)
- Collect urine for TDF testing for adherence

- Test for HIV
- Record participant's adherence to treatment regimen.
- Provide additional 28-days (1-month) supply of medication to the participant
- Provide final HIV prevention counselling to participant.
- Conduct endline questionnaire
- Inform of continued follow-up support to care by the national program
- Visit 6 will require between 1.5 and 2 hours to complete

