| Syphilis testing                                            | X                               |                  |                  |                     |                  |                     |                  | X                           |
| HBsAg test                                                  | X                               |                  |                  |                     |                  |                     |                  | X                           |
| Serum creatinine test                                       | X                               |                  |                  |                     |                  |                     |                  | X                           |
| HIV test                                                    | X                               |                  | X                |                     |                  | X                   |                  | X                           |
| Schedule study visits                                       | X                               |                  |                  |                     |                  |                     |                  |                             |
| Provide 28 days of emtricitabine/tenofovir disoproxil       |                                 | X                | X                | X                   | X                | X                   | X                | X                           |
| Randomization 2 (Omni-channel PrEP Champion)                |                                 | X                |                  |                     |                  |                     |                  |                             |
| Record vital signs                                          |                                 |                  |                  | X                   |                  | X                   |                  | X                           |

| Procedures                                        | Recruitment and Screening Visit | Baseline Visit 0 | Visit 1 (refill) | Follow-up (Visit 2) | Visit 3 (refill) | Follow-up (Visit 4) | Visit 5 (refill) | Final Study Visit (Visit 6) |

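### The visit schedule has no vital signs before the first PrEP dose; blood pressure and weight are first recorded at Visit 2, about Day 60

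*Protocol*

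**What the plan says.** Section 7.1.1 of the protocol lists, among the study-specific procedures: "A brief physical examination for vital signs, including height, weight and blood pressure will be completed by the clinical team". It does not say at which visit.

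Timing appears in two other places, and they agree.

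- The schedule of events (7.3.6) has a row "Record vital signs", marked at Visits 2, 4 and 6 and blank at Screening and at Visits 0, 1, 3 and 5.
- The visit lists give "Record vital signs, results of screening for Syphilis or other health conditions" at Visit 2, "Record vital signs, or other health conditions" at Visit 4 and "Record vital signs or other health conditions" at Visit 6.

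The screening list (7.3.1) introduces its eligibility examinations with "Specifically we will perform" and then names HIV, HBsAg, and blood for creatinine and syphilis. The Visit 0 list (7.3.2) contains "Directly observe the first dose of emtricitabine/tenofovir disoproxil being taken" but no vital signs. Visit 1 has "Check on adverse effects", again without vital signs. An early termination visit (7.3.5) repeats the final-visit procedures if the woman is willing.

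Section 8.3 treats a medical condition already there at screening as baseline, and counts it as an adverse event only if it gets worse during the study.

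**The concern.** The protocol defines adverse events for existing conditions by change from the state at screening, yet for blood pressure and weight it schedules no measurement of that state. If staff follow the schedule, the first reading comes about two months into treatment. A raised blood pressure at Visit 2 could then be undiagnosed hypertension that was there all along, known blood pressure elevation that has worsened, or something new. Only the woman's history can separate these. The hypertension exclusion in 5.2 does not help, because it rests on a reported past diagnosis and not on a measurement.

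A reading missed before the first dose cannot be recovered afterwards. What is at stake is the quality of the safety record, not the trial's efficacy conclusions.

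**Working it through.** There is no figure of the plan's own to reproduce. The check is to read the schedule column by column against the visit lists.

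**Vital signs by visit**

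| Visit | 7.3.6 | Visit list | Relative to first dose |
|---|---|---|---|
| Screening | no | not named (7.3.1) | before |
| Visit 0 | no | not named (7.3.2) | first dose given here |
| Visit 1, Day 30 | no | not named (7.3.3) | after |
| Visit 2, Day 60 | yes | named (7.3.3) | after |
| Visit 3, Day 90 | no | not named (7.3.3) | after |
| Visit 4, Day 120 | yes | named (7.3.3) | after |
| Visit 5, Day 150 | no | not named (7.3.3) | after |
| Visit 6, Day 180 | yes | named (7.3.4) | after |

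Vital signs are marked in 3 of 8 columns, and in 0 of the 2 columns up to and including the first dose. Since the table and the lists match at every visit, a misread table does not explain the gap.

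**Comparison with the other repeated health measurements in 7.3.6**

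- HIV: Screening, Visits 1, 4 and 6
- HBsAg: Screening, Visit 6
- Creatinine: Screening, Visit 6
- Syphilis: Screening, Visit 6
- Vital signs: Visits 2, 4 and 6

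Four of the five have a Screening entry; vital signs is the only one that starts after the drug. Urine TDF and adverse event evaluation also start after dosing, but they have no meaningful pre-drug value and are left out of the count.

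**Time and exposure at the first reading**

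- Visit 2 window: 60 − 7 = Day 53 to 60 + 7 = Day 67.
- Tablets dispensed before Visit 2 to a woman who attends Visits 0 and 1: 28 + 28 = 56.

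A woman with an early termination visit may be measured sooner, but still after dosing. A woman lost before Visit 2 without such a visit has no reading at all. The protocol does not give the numbers expected in these groups.

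**Where the values are used.** No endpoint in 4.3.1 to 4.3.3 uses blood pressure or weight. No criterion in 5.2 is stated in terms of a measured blood pressure or weight. The halting rule in 8.5 counts serious adverse events. The baseline rule in 8.3 is the place where a pre-dose reading would bear on a decision.

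**The case against.** The strongest reply is that 7.1.1 already implies an entry examination. It sits between the medical history, which is marked only at Screening, and blood tests that all have Screening entries, and it includes height, which makes most sense at entry. On that reading the 7.3.6 row is the follow-up repeat. The schedule is also not a full inventory: pill counts, for example, have no row. This may well be the intent, and it means 7.1.1 does not contradict the schedule. But no visit list or schedule entry carries that intent out, and staff working from the schedule would omit the reading. The correction is the same either way.

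Second, the screening sub-list covers examinations needed for eligibility, and HIV, HBsAg and creatinine are there because they are exclusion tests. Vital signs would not be expected in that sub-list, and among the four only syphilis is a like-for-like comparison. This weakens the four-of-five count as evidence of an oversight. It does not supply a pre-dose reading, since no other line for Screening or Visit 0 names one.

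Third, 8.2.2 says that doubtful observations should be reported as adverse events, so an unclear reading would not be lost. This stands, and it limits the harm. It settles whether to report, but not whether the finding was there before the drug.

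Fourth, blood pressure and weight change are not among the drug risks named in 2.4.1, and every randomised group receives the same drug, so no planned comparison of delivery or support depends on these readings. This also stands, and it is why the point is minor.

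Finally, the manual of procedures or the national PrEP framework may schedule the examination. Neither is shown, so the conclusion is limited to the protocol.

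**Conclusion.** The concern holds, as a minor one. As written, the protocol schedules no vital signs before the first dose; for a woman on schedule the first reading is at Day 53 to 67, after 56 tablets have been dispensed. The consequence is confined to classifying events defined by blood pressure or weight under 8.3, where the baseline would rest on history alone. Sample size, power, endpoints and halting are unaffected, and the named renal and hepatitis B risks are tested before dosing.

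This assumes that sites follow 7.3.6 and the visit lists, and that no document outside the protocol adds an entry examination.

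**What to change.** Mark vital signs (height, weight, blood pressure) at Visit 0 in 7.3.6, and add a line to 7.3.2 placing the reading before the observed first dose. In 8.3, name that reading as the baseline for events defined by blood pressure or weight. The sentence in 8.3 is needed with this choice because that section now refers to the time of screening. The alternative is to mark Screening in 7.3.6 and add the line to 7.3.1.

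The cost is one schedule mark, one line in a visit list, one form field and one sentence, for a measurement that 7.1.1 already commits to and staff already take at three visits. In the field it is a few extra minutes per woman: about 160 women at Visit 0, or up to 1204 at Screening. Visit 0 is the cheaper choice.

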**Primary objective 3:** To assess barmaids' preferences, willingness to use, feasibility and factors for uptake of long-acting injectable HIV PrEP in Ubungu municipality, in-depth interviews will be conducted with barmaids who have used PrEP for about six months and those who have not been involved with PrEP intervention to learn about their preferences for delivery of and willingness to use long-acting injectable PrEP and factors that contribute to uptake of long-acting injectable PrEP. Also, Key informant interviews will be conducted with different stakeholders working in HIV interventions to understand their views on the feasibility of implementing long-acting injectable PrEP among barmaids, challenges in the implementation of PrEP pills programs and their preferences for service provision and factors that contribute to uptake of long-acting injectable PrEP.

**Secondary objective 1:** To determine whether being supported by an omni-channel (physical and virtual) PrEP Champion, who provide support and information to clients, improves adherence and retention. Depending on feasibility (owning a smartphone) and preferences of the participants, they will receive physical and/or virtual support from the responsible PrEP Champion who will regularly share standardized informative media with the participants to improve their PrEP knowledge and provide adherence support. We propose to evaluate whether the program omni-channel PrEP Champions is an effective and feasible method to improve

adherence in a high-risk population. We will use self-reported adherence as our effectiveness outcome for this objective, to capture drug use across the whole study period, rather than the shorter window captured by urine-based testing. We will use in-depth interviews with respondents, and key informant interviews with the PrEP Champions, to evaluate the feasibility of omni-channel PrEP Champions, including with respect to rolling it out more widely.

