### **4.3.3 EXPLORATORY ENDPOINTS**

1. Level of HIV-related knowledge, including PrEP
2. Characteristics of those accepting and declining to initiate PrEP
3. Proportion of those initiating PrEP retained in care at each study visit
4. Proportion of those initiating PrEP reporting >85% adherence at each study visit
5. Proportion of those initiating PrEP reporting side-effects
6. Number of HIV seroconversions at each study visit
7. Change in number of sexual partners reported in past 30 days from initiation to each study visit
8. Proportion of women reporting consistent condom use at baseline and final visit
9. Proportion of those initiating PrEP with STI symptoms at each study visit
10. Proportion of those initiating PrEP receiving a routine follow-up.
11. Proportion of those initiating PrEP declining being part of the omni-channel PrEP Champions intervention at baseline and at each study visit.
12. Proportion of those initiating PrEP with Tenofovir urine levels compatible with weekly dosing, dosing in the past 2 to 3 days, and dosing within the past 24 hours.

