## 9.2 STATISTICAL HYPOTHESES

**Primary endpoint 1:** We hypothesize that the proportion of eligible individuals who agree to initiate PrEP and are observed to take the first tablet on Day 0 will be higher in the workplace-based group than in the facility-based group. The null hypothesis is of no difference between the community- and facility-based groups; this will be a superiority comparison.

**Primary endpoint 2:** We hypothesize that the urine level of TDF in those enrolled in the workplace-based study group will be significantly higher than that in the facility-based group when measured at the 6-month post-initiation visit. The null hypothesis is of no difference between the community- and facility-based groups.

**Secondary endpoint 1a:** We hypothesize that the average number of refills made per initiated participant in the workplace-based group across the 6 months of study follow-up (i.e. at visits 2 and 3) will be higher than in the facility-based group. The null hypothesis is of no difference between the community- and facility-based groups; this will be a superiority comparison.

**Secondary endpoint 1b:** We hypothesize that the adherence per participant in the PrEP Champions intervention group across the 6 months of study follow-up (i.e. at visits 2 to 5) will be higher than that of participants in the national standard of care control group. The null hypothesis is of no difference between the two groups; this will be a superiority comparison.

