## 9.4 Measures to Minimize Bias

### 9.4.1 ENROLLMENT/ RANDOMIZATION/ MASKING PROCEDURES

The study will involve a cluster two sequential, independent randomized study. First, bars will be randomized at screening into either workplace-based or facility-based PrEP initiation and follow-up. Second, individuals will be concurrently randomized into either PrEP Champion intervention or no- PrEP Champion intervention for adherence and follow-up support. Anticipating that PrEP initiation will be approximately 10% in the facility-based arm vs. 25% in the workplace-based arm based on previously published studies in the region, we will randomize to either the facility-based arm or the workplace-based arm in a 2:5 ratio in order to obtain balance for ascertaining the second, more expensive outcome, 6-month adherence. If, as hypothesized, PrEP initiation is higher in the community- than the facility-based groups, our first primary outcome is powered to account for this unbalanced design. Under our primary hypothesized difference, in which 10% of those offered facility-based PrEP and 25% of those offered workplace-based PrEP join our study, the four study groups for our second primary outcome and secondary outcomes will look as in the table below:

|                                                               | Workplace-based
PrEP provision | Facility-based
PrEP provision |
|---------------------------------------------------------------|-----------------------------------|----------------------------------|
| Omni-channel PrEP Champion intervention
for PrEP adherence | 40                                | 40                               |
| National standard of care for PrEP adherence                  | 40                                | 40                               |

Individuals who discontinue the study early will not be replaced; since the primary endpoint is measured as urine level of TDF, they will automatically be assigned the value of zero. This non-replacement will not affect power, since by assigning discontinuing individuals a final outcome value no loss of sample size results.

The study will necessarily not be blinded. From the participants' side they will know which of the four study groups they are in based on the intervention they receive; from the investigators' side they will know who is receiving and not receiving workplace-based PrEP delivery and is part of an Omni-channel PrEP Champion intervention group.

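### Self-reported adherence is scored by the hour at which pills are taken, although it serves as the PrEP Champion outcome in order to measure drug use

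*Protocol*

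**What the plan says.** Protocol section 7.1.1 lists three adherence measures at each two-monthly visit: self-report, pill count and the urine TDF assay. It defines the first as "self-reported adherence in terms of percentage of doses taken at the agreed time of day on the correct day". A dose must therefore satisfy both the hour and the day to count. This is the only definition of the self-report score in the protocol.

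Section 3, secondary objective 1 (PrEP Champion), states the purpose of the score: "We will use self-reported adherence as our effectiveness outcome for this objective, to capture drug use across the whole study period". Section 9.2, secondary endpoint 1b, carries this into a superiority hypothesis: "We hypothesize that the adherence per participant in the PrEP Champions intervention group across the 6 months of study follow-up" is expected to exceed that of the control group.

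Other sections describe the measure or the dosing without reference to the clock:
- Section 6.1.10: "Dose/adherence monitoring will be based on self-reported use evaluated every month, as well as pill counts of remaining pills at each visit".
- Section 6.1.5: one tablet "once daily taken orally with or without food", with no hour named.

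Section 4.3.3 applies a threshold to reported adherence as exploratory endpoint 4: "Proportion of those initiating PrEP reporting >85% adherence at each study visit".

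**The concern.** The declared target is drug use, but the stated rule measures drug use and punctuality together. A pill swallowed a few hours late on the right day scores the same as a pill not swallowed. Two consequences follow.

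First, the score understates dose-taking for any woman who is late, so the >85% proportion is lower than the share who took more than 85% of their pills.

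Second, and more important, the Champion comparison can respond to timing alone. Section 4.1 describes the Champions as helping participants keep to their PrEP routine through meetings, messages and calls. Such support could plausibly move the hour of pill-taking as well as, or instead of, the number of pills taken. A shift in the hour alone would then be read as an effect on drug use. The trial is unblinded and the outcome is self-reported, which is a further reason to keep a component unrelated to drug use out of the score.

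**Working it through.** The protocol states no power, effect size or late-dose frequency for self-reported adherence, so there is no planned figure to reproduce. The checks are arithmetic on the definition, followed by illustrations on assumed inputs.

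**Inputs from the protocol.** Each supply is 28 doses (section 7.3.2: "provide 28 (1 month) days of emtricitabine/tenofovir disoproxil"). That gives 28 doses for the monthly interval in section 6.1.10, 56 for the two-monthly interval in section 7.1.1, and 6 × 28 = 168 over six months. The Champion comparison is 80 v 80, from the 40 + 40 cells at each level in the section 9.4.1 table. Tests are two-sided at 5% (section 10.5.1).

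**1. Scoring by hand.** Score = on-time doses / doses due, with every pill taken on its day.

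| Doses due | Late | Score | Above 85%? |
|---|---|---|---|
| 28 | 4 | 24/28 = 85.7% | yes |
| 28 | 5 | 23/28 = 82.1% | no |
| 56 | 8 | 48/56 = 85.7% | yes |
| 56 | 9 | 47/56 = 83.9% | no |
| 168 | 25 | 143/168 = 85.1% | yes |
| 168 | 26 | 142/168 = 84.5% | no |

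The ordering of women can also reverse. One who takes 56 of 56 with 11 late scores 45/56 = 80%. One who takes 48 on time and misses 8 scores 48/56 = 86%.

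**2. Share above the cut-off.** Assume 56 independent doses, 95% of doses taken, and a fraction L of those late. On-time doses are then binomial with probability 0.95 × (1 − L), and the cut-off requires at least 48.

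| L | On-time probability | Share above 85% |
|---|---|---|
| 0 | 0.950 | 99.8% |
| 5% | 0.9025 | 91% |
| 10% | 0.855 | 57% |
| 15% | 0.8075 | 22% |

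Identical women and independent doses are simplifications. Real spread between women would soften these contrasts.

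**3. Champion comparison with equal drug use.** This is a simulation of 80 v 80 women with 168 doses each. Dose-taking is drawn from Beta(18, 2), mean 90%, in both groups. The late fraction is drawn per woman from a beta distribution whose mean may differ between groups. The comparison is a t-test on the individual scores. The expected difference is 0.90 × (difference in late fraction): 0.90 × 0.10 = 9 points, or 0.90 × 0.05 = 4.5 points.

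| Mean late fraction | Spread of late fraction | Score SD | Rejection, on-time rule |
|---|---|---|---|
| 15% v 25% | beta precision 8 | about 13 points | about 99% |
| 15% v 25% | beta precision 2 | about 21 points | about 75% |
| 15% v 20% | beta precision 8 | about 13 points | about 59% |
| 15% v 15% | beta precision 8 | about 12 points | 5% |

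When any dose taken on the correct day counts, rejection is about 5% in every row.

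**4. Cross-check by the two-mean power formula, 80 v 80.** A difference of 10 points in mean on-time share is declared significant with probability 0.99, 0.89 or 0.72 at SD 15, 20 or 25. A difference of 5 points gives 0.56, 0.35 or 0.24.

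**The case against.** The case for leaving the definition alone has several parts.

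- **It is a percentage, not a classification.** This stands. A reader might infer that a woman who takes some pills late is scored as non-adherent. The protocol does not say so: her score falls, and a yes/no label arises only under exploratory endpoint 4, from 5 of 28 or 9 of 56 late doses. That endpoint does not itself cite section 7.1.1. Applying the 7.1.1 definition there is the natural reading, because no other is given.
- **The wording is a brief procedure description, and the questionnaire is not shown.** This stands in part. A broad agreed period, such as the evening, would lose few same-day doses. But the sentence names both time and day and allows no tolerance, and it differs from section 6.1.10. A questionnaire written to follow it would ask the wrong question.
- **Other measures would reveal the problem.** Partly true. Pill count does not depend on the hour and is collected at the same visits. Refill counts are also compared between Champion groups (sections 4.3.2 and 10.5.3) and are unaffected by pill timing. Neither is the outcome that section 3 names for effectiveness on adherence. The urine assay does not settle it either: it reflects recent use, is run at months 2 and 6 only, and does not count individual doses.
- **The size is built in by assumption.** This stands. A reader might take the 99% as the false-positive rate of the Champion comparison. It is not: it follows from an assumed timing gap of 15% v 25% and a modest spread. No document figure supports that gap, and nothing shows that Champions would change timing while leaving dose-taking unchanged.
- **Punctual dosing is a legitimate, stricter definition of adherence.** It may be, but it is not the quantity that section 3 says the score is there to capture. Nor do the documents support a claim that late takers were fully protected, and none is made here.

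**Conclusion.** The point holds as a mismatch between a stated purpose and a stated measurement rule. Followed literally, section 7.1.1 treats a same-day late dose as a missed one, while sections 3 and 6.1.10 want self-reported use. The arithmetic against the >85% cut-off needs only literal scoring. The effect on the Champion comparison is conditional: it requires timing to differ between the groups. If timing is equal, the test keeps its 5% error rate and the remaining harm is a score that understates dose-taking. If timing differs, the illustrations run from about 59% to about 99% rejection with no difference in drug use, and from 0.24 to 0.99 across the wider set of assumed differences and SDs. All timing inputs are assumptions, so no single figure should be quoted as the expected error. The outcome is secondary and the correction is small, so this should be fixed but does not threaten the primary comparisons.

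**What to change.** In section 7.1.1, define self-reported adherence as the percentage of prescribed daily doses taken on the correct day, at any hour. Use that definition for secondary objective 1, for endpoint 1b in section 9.2 and for the >85% item in section 4.3.3. If timing is of interest, collect the percentage taken at the agreed time as a separate descriptive item. Reconcile sections 3, 6.1.10 and 7.1.1 so that all three describe the same score.

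The cost is one sentence and one questionnaire item reworded or split. This is best done before the questionnaire is fielded, because a single combined answer cannot be separated afterwards. The downside is that timing leaves the effectiveness score. The change concerns measurement only and leaves the dosing instruction as it is.
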